### Prediction of RT response in patients with CIBP

Palliative radiation therapy (RT) is a major treatment modality for cancer induced bone pain (CIBP), often together with opioids and co-analgesics [10]. Unfortunately, not all patients experience pain relief after RT. Complete pain response is reported in about one quarter of the patients, and partial pain response in 40–60% [11, 12]. Median time to pain response is 1 to 4 weeks [13]. RT are in most cases not associated with severe adverse effects, but nausea and vomiting is reported in up to 77% of patients [14], and pain-flares during and after RT is reported by up to one third of the patients [15, 16]. Diarrhoea, skin reactions, lethargy and tiredness are also potential adverse effects after RT [11].

Based on a relative high number of patients not responding to RT, time to treatment effect and the risk of potential side effects it is important to identify potential predictors for RT response. Former RT trials have used different pain assessments and different definitions for RT response. An international consensus on endpoints in RT trials were first published by Chow et al. in 2002 and updated in 2012 and have resulted in more comparable RT trials [17, 18]. Two recent papers on rather large patient materials found that patients with breast or prostate cancer and higher performance status were more likely to respond to RT. High baseline pain scores, the use of morphine, absence of visceral metastases and younger age were also associated with RT response in one out of the two papers [19, 20].

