Imaging techniques may also be helpful to predict RT response. Two studies have demonstrated that low uptake on FDG PET-CT before RT predicted better RT response [21, 22]. MRI have also been proposed to predict RT response, but the published results are so far inconsistent [23, 24]. In addition both PET and MRI is time and economically difficult to establish as routine care. Biomarkers such as urinary osteoclast markers have been proposed to predict RT response in patients with bone metastases [25, 26], but this association is not present in all trials [27]. Elevated C-reactive protein (CRP) levels are related to more advanced disease in cancer patients that undergo palliative RT, but as far as we know no studies demonstrate a relationship between the level of CRP or other inflammatory markers and RT response in patients with CIBP [28]. Previous published literature on clinical predictors for response to RT has also no information about radiographic appearance of metastases like sclerotic/osteolytic metastases, soft tissue expansion outside bone, other cancer related symptoms or biomarkers as potential predictors.

Thus, there is still not enough information to predict which patients who are likely to respond poorly, and consequently should not receive RT. To identify patients who have increased likelihood of successful analgesia from palliative RT would improve cancer pain management.

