#### Cancer induced bone pain and the role of inflammation

Based on results from pre-clinical studies several inflammatory mediators are proposed to play an important role in CIBP. The pro-inflammatory interleukin (IL)-1β, IL-6 and tumor necrosis factor (TNF)-α are associated with nociception in animal models of bone cancer [31, 32]. Other inflammatory mediators, including chemokines such monocyte chemoattractant protein (MCP)-1, macrophage inflammatory protein (MIP-1)α, and the anti-inflammatory cytokine transforming growth factor (TGF)β, are upregulated in animal models of bone metastases, and receptors for cytokines are also present on the osteoclast surface. The release of inflammatory cytokines from tumor cells may therefore contribute to osteoclast activation with CIBP as a consequense [8, 33]. Some studies have demonstrated a potential role of inflammation (CRP, IL-6) for general cancer pain [34–36]. but as far as we know there are no published clinical trials on inflammation in relation to CIBP.

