### The palliative radiotherapy and inflammation study (PRAIS)

As cancer treatment develops, a wider range of treatment options are available to each patient, and the need for tools to determine treatment response arises to select the right individual treatment. The primary aim of the PRAIS study is to combine clinical and biomarker predictors to predict the response to RT for patients with CIBP.

The availability and indications for new cancer therapeutics that modulates the immune system in order to delay development and even cure cancer have increased the last years, and a better understanding of the role of systemic inflammation in relation to cancer and cancer associated symptoms are of interest when the field of immunotherapy develops. To better understand complexity of systemic inflammation one need to extrapolate knowledge from pre-clinical studies to clinical studies with a robust study design. Secondary aims of the PRAIS study are, therefore, in a longitudinal study to explore the relationship between cancer related symptoms and inflammatory biomarkers during a one-year follow up.

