*Statistical method*: Clinical variables (see previous chapter) and CRP will be included in a multivariate logistic regression model to predict potential factors for response to RT. The model will be adjusted by study centre. Regression diagnostics will be performed for all analyses adding interactions terms if necessary. Significant variables from the multivariable model will be presented as a response-score to determine the likelihood of response to RT. Second, we will perform analyses on inflammatory biomarkers and bone biomarkers correlated with response to RT. Only inflammatory biomarkers and bone biomarkers with levels of serum concentrations above the detection threshold and which have a variability between measurements will be analysed with a multivariate logistic regression model with response to RT as the dependant variable. Finally, an integrated regression model with response to RT including both the significant clinical variables and significant biological biomarkers will be conducted if appropriate based on results from the previous analyses.

**Research question 2:** Which inflammatory biomarkers are associated with change in pain intensity in patients with CIBP?

*Objective*: To investigate the correlation between pain intensity and inflammation. Patients included in the PRAIS study all have CIBP and will receive a standardized intervention expected to give pain relief in about 60% of the patients. This study can explore if there is a longitudinal relationship between changes in pain intensity and the detected level of inflammatory biomarkers.

*Outcome*: Serum concentrations of inflammatory biomarkers as described above associated with changes in pain intensity as measured by average pain intensity and worst pain intensity last 24 h (NRS 0–11) for a maximum of 1 year follow-up.

*Statistical method*: Longitudinal data analysis with repeated measurements using a liner mixed effect model or generalized estimating equation (GEE).

**Research question 3:** Which inflammatory substances are associated with cancer cachexia?

*Objective*: To gain insight into the role of inflammation in cancer cachexia.

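### Research question 1 admits biomarkers to the integrated model on a test that ignores the clinical predictors, so a marker with real added value can be screened out and not recovered

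*Protocol article*

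**What the plan says.** The Background section on the PRAIS study sets the primary aim: to "combine clinical and biomarker predictors to predict the response to RT for patients with CIBP". Under Outcome and statistical analyses, Research question 1 pursues it in three steps.

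1. "Clinical variables (see previous chapter) and CRP will be included in a multivariate logistic regression model to predict potential factors for response to RT". Adjustment for study centre is stated with this model.
2. Inflammatory and bone markers that are detectable and vary between measurements "will be analysed with a multivariate logistic regression model with response to RT as the dependant variable". No clinical variable is named as a covariate.
3. "Finally, an integrated regression model with response to RT including both the significant clinical variables and significant biological biomarkers will be conducted if appropriate".

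A marker other than CRP therefore meets the clinical variables only in step 3, and only if it was significant in step 2. High-sensitivity CRP also stands among the inflammatory markers in Table 2, so the same substance appears on both sides of the split.

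**The concern.** A combined prediction needs to know what a marker adds once the clinical data are known. Step 2 asks something else: whether the marker is associated with response given the other markers, with clinical state ignored. The article's own background gives reasons why the two answers can differ.

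- Severity: "Elevated C-reactive protein (CRP) levels are related to more advanced disease in cancer patients that undergo palliative RT", and the same section reports better response with higher performance status. The section on cancer-related symptoms and inflammation adds that it is hard to tell whether inflammation merely reflects severity of disease.
- Pain: "Some studies have demonstrated a potential role of inflammation (CRP, IL-6) for general cancer pain", and "High baseline pain scores, the use of morphine, absence of visceral metastases and younger age were also associated with RT response", the latter in one of the two papers cited.

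Two errors are possible. A marker with its own effect can look inert in step 2 because a correlated clinical factor pulls the other way; it is then dropped, and step 3 never sees it. Conversely, a marker with no effect of its own can look predictive in step 2 because it stands in for severity.

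**Working it through.** **Inputs from the article.** Up to 29 clinical variables; 600 patients; up to 20% loss to follow-up; about 60% response; 33 candidate markers by count of Table 2 (29 inflammatory, 4 bone) before filtering. The article's figure of 290 reproduces as 10 × 29. Evaluable patients: 600 × 0.8 = 480. Non-responders: 480 × 0.4 = 192.

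**Assumptions.** The article gives no correlations, effect sizes or significance level. The simulations assume two-sided 5% tests, 10 or 20 markers left after filtering, and effects per SD.

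**Mechanism.** To a first approximation, the marker-only coefficient is b(marker) + Σ r × b(clinical factor), on the log-odds scale. With b(marker) = -0.3 (odds ratio 0.74) and ln 1.5 = 0.405:

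- pain path, r = 0.3: -0.3 + 0.3 × 0.405 = -0.18, so the signal shrinks;
- pain path plus an equal and opposite severity path: -0.3 + 0.12 - 0.12 = -0.30, unchanged;
- severity path only: -0.3 - 0.12 = -0.42, so the signal grows;
- no own effect, severity odds ratio 0.60 (ln = -0.511), r = 0.3: 0.3 × (-0.511) = -0.15, a signal where none exists.

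**Marker with a true adjusted effect: share of runs passing (480 patients, 29 clinical variables, log odds ratio -0.3).**

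| Scenario | Marker-only screen, 10 / 20 markers | Clinical variables in the model, 10 / 20 markers |
|---|---|---|
| Pain odds ratio 1.5, r = 0.2 | 47% / 39% | 73% / 64% |
| Same, r = 0.3 | 33% / 28% | 71% / 61% |
| Same, r = 0.4 | 22% / 19% | 71% / 58% |
| Pain path plus weaker severity path (1/1.25), r = 0.3 | 63% / 57% | 73% / 68% |
| Pain path plus equal severity path (1/1.5), r = 0.3 | 79% / 80% | 73% / 74% |
| Severity path only, r = 0.3 | 98% / 98% | 77% / 75% |
| Uncorrelated | 73% / 60% | 75% / 61% |

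The rows come from separate simulation sets, so compare within a row. Another run of the pain-only case with 10 markers gave 52% (r = 0.2) and 19% (r = 0.4), against about 80% adjusted. A set with marker odds ratio 0.7 gave, at r = 0.5, 65% against 91% (pain odds ratio 1.3) and 24% against 89% (pain odds ratio 1.6).

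**Does step 3 recover a masked marker?** No. With pain odds ratio 1.5 and r = 0.3, the whole three-step procedure kept the marker in 35% (10 markers) or 29% (20) of runs.

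**Null proxy: share passing step 2.** One factor with odds ratio 1.5 and r = 0.3: 21% / 16% (10 / 20 markers). Four factors with odds ratio 1.25 and r = 0.2: 34% / 29%. Across runs at such modest correlations the range was about 16-48%. A set with r from 0.3 to 0.7 and severity odds ratio 0.75 or 0.60 ran from 13% to 95%. With the clinical variables in the model the rate is about 4-7%. After step 3, false retention is about 2-7% in most settings and about 10% with four factors at r = 0.3.

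**The case against.** Four arguments carry weight.

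- **Step 3 re-tests admitted proxies.** It sets each one beside the significant clinical variables and removes most. A reader might infer that the final model will fill up with severity proxies; the figures above do not support that. The false-positive problem mainly concerns how step 2 is reported, or a study in which step 3 is not run, which its conditional wording allows.
- **Masking needs a particular sign pattern.** The marker's own effect must oppose its path through the clinical factor. The article knows of no study relating inflammatory markers to response, and the pain link comes from one of two papers. The severity route can offset the pain route in the same marker. A reader might infer a general, large loss of power; that is one corner of a range that includes no loss and gain.
- **Step 2 answers a legitimate question.** An unadjusted association is worth describing, and the Discussion calls the inflammation work more explorative. But step 2 is also the gate to the integrated model, and there the unadjusted question is the wrong one.
- **Clinical covariates are not expressly excluded from step 2.** That is so, and covariate lists are often left to an analysis plan. The natural reading is still that they are absent: only markers are named, and a separate integrated model would otherwise have little purpose. If adjustment is intended, one sentence settles the matter.

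**Conclusion.** The concern stands as a mismatch between the aim and a stated selection rule. Its firm part is structural: a marker other than CRP that fails a test made without the clinical variables cannot return, whatever it would have added to them.

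The size is conditional. For a marker masked by baseline pain alone, at correlations of 0.2 to 0.4 and the assumed effects, the chance of admission is roughly 20-50% instead of about 60-80%. A weaker opposing severity path cuts the loss to about 10 points, an equal one removes it, and when the paths reinforce each other the planned screen admits more. All of this rests on assumed correlations and effects. The change is worth making because it is cheap and touches the primary question, not because a large loss has been shown for this study.

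**What to change.** Make the admission test conditional. Admit a marker to the integrated model on a test adjusted for the pre-specified clinical variables and study centre, by one of three routes: each marker added singly, a block likelihood-ratio test, or a penalised model. Control the false-discovery rate over the up to 33 markers; at 5% each, 33 × 0.05 = 1.65 null markers would pass on average. Report clinically adjusted odds ratios. Keep the marker-only model, labelled as descriptive and unadjusted for clinical state. State whether high-sensitivity CRP belongs to step 1 or step 2, and under what condition the integrated model is fitted.

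Costs: no new data, patients or assays. There are fewer non-responders per term: 192/29 = 6.6 for the clinical set and 192/30 = 6.4 with one marker added, before CRP and centre. All 33 markers together would give 192/62 = 3.1, so one unpenalised model with everything is not advisable. Missing clinical covariates will remove some complete cases. If markers are tested singly, they are not adjusted for one another until the integrated model. Adjustment cost no power in the uncorrelated scenario (73.4% against 75.0% with 10 markers, 59.9% against 61.3% with 20).

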### Cancer related symptoms and the role of inflammation

In recent years there has been an increased interest among researchers to understand the correlation between the immune system and development of cancer and cancer-related symptoms. Inflammation is present in the majority of patients with advanced cancer [29], and it is therefore difficult in cross sectional studies to establish if inflammation is simply associated with severity of the cancer disease, or whether inflammation itself elicits symptoms and can be a target to reduce symptoms like pain, depression or cachexia [30].

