*Outcome*: Cachexia is defined as a) weight loss > 5% over past 6 months (in absence of simple starvation); or b) body mass index (BMI) < 20 and any degree of weight loss > 2%; or c) appendicular skeletal muscle index consistent with sarcopenia (males < 7・26 kg/m2; females < 5・45 kg/m2) and any degree of weight loss > 2% [38]. Cachexia severity is assessed as degree of weight loss and EORTC QLQ C15 PAL physical function and appetite loss.

*Statistical method*: Fist, we will perform a cross-sectional analysis in the baseline parameters using a logistic regression with cachexia as outcome, and the various inflammatory markers as explanatory variables. Second, we will investigate the association between changes in inflammatory markers over time and cachexia severity using mixed linear modelling.

**Research question 4:** Which inflammatory substances are associated with depression in cancer patients?

*Objective*: To explore the associations between serum concentrations of inflammatory substances and depression.

*Outcome*: Depression is measured by the PHQ-9 questionnaire [57]. The PHQ-9 includes 9 items identical to the diagnostic criteria (i.e. the depression symptoms) for depression disorder. For the purpose of these analyses we will use depressive disorder as defined by the PHQ-9 recommended sum score calculation, and symptom by symptom in the PHQ-9 score in associations of serum concentrations of inflammatory biomarkers during a period of 1 year form inclusion.

*Statistical method*: We will use repeated measurements and a linear mixed effect model to perform the analyses.

**Research question 5:** Which are the clinical predictors and biomarker predictors of development of cachexia in patients with metastatic cancer disease?

*Objective*: To obtain demographic and clinical data and biomarkers in a homogenous population of patients with metastatic cancer, and within a prospective, longitudinal follow-up study observe which factors predicting the development of severe cachexia during one-year follow-up.

*Outcome*: Cachexia is defined as for research question 3.

*Statistical method*: As the purpose is to evaluate development of cachexia, only patients without cachexia at baseline will be included in this analysis. A Cox regression will be used to evaluate baseline predictors of cachexia development.

**Research question 6**: What is the relationship between pain reduction and depression in patients receiving RT for CIBP?

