### Expected limitations

As for all studies on palliative cancer patients we expect the number of drop-outs and missing data to be relatively high. A reason for drop-out before evaluation of treatment response may be that the patients are too sick or because of high symptom burden. These patients cannot be included in the predictive analyses as they are not missing at random and may bias the results. The patient inclusion is also for practical reasons not consecutive and the sample size of 600 do not allow for a validation sample analyses. Also, in order to assess the adverse effects from RT, a day-to-day evaluation of symptoms after RT would have given important information but were not performed in order to simplify data collection for the patient population.

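### RQ2 and RQ6 ask about change within patients, but the stated longitudinal models do not separate this from differences between patients

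*Protocol article*

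**What the plan says.** All references are to the protocol article. Under Outcome and statistical analyses, Research question 2 describes its target in three ways. The question is "Which inflammatory biomarkers are associated with change in pain intensity in patients with CIBP". The objective opens with "To investigate the correlation between pain intensity and inflammation" and continues "This study can explore if there is a longitudinal relationship between changes in pain intensity and the detected level of inflammatory biomarkers". The method is one line: "Longitudinal data analysis with repeated measurements using a liner mixed effect model or generalized estimating equation (GEE".

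Research question 6 treats radiotherapy as something close to an experiment: it shifts pain, and the consequence for depression is observed. Its method is a linear mixed model on repeated measurements.

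The Background gives the reason for following patients over time. Inflammation is common in advanced cancer, and "it is therefore difficult in cross sectional studies to establish if inflammation is simply associated with severity of the cancer disease" or whether it elicits the symptoms itself. The Methods paragraph of the Abstract words the secondary aim as association with changes in pain intensity, cachexia and depression over one year. The Timeline section sets six assessments: baseline and weeks 3, 8, 16, 24 and 52.

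**The concern.** A time-varying exposure such as a cytokine level carries two kinds of information. One is that some patients run higher than others on average. The other is that the same patient is higher at one visit than at another. Only the second bears on change. The first is the cross-sectional comparison, in which sicker patients may have both more inflammation and more symptoms.

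A random-intercept model or a GEE with the raw exposure as a single covariate returns one slope that is a weighted average of the two. The repeated measurements do not remove the cross-sectional part. If that slope were read as the answer to Research question 2 or 6, the confounding by severity that motivates the longitudinal design would return under the name of change.

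**Working it through.** **Plan figures.** The protocol gives no sample size, power or variance components for these research questions, so there is no figure to reproduce. The variance inputs below are assumptions.

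**Closed form.** Give exposure and outcome unit variance. With exposure intraclass correlation ICCx, the between-patient variance is ICCx and the within-patient variance is 1 - ICCx; likewise ICCy for the outcome. For T visits per patient:

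- within-patient information: W = (T - 1)(1 - ICCx)
- between-patient information: B = T·ICCx + (1 - ICCx)
- weight the random-intercept model gives to B: psi = (1 - ICCy) / [(1 - ICCy) + T·ICCy]
- share of the between-patient slope that appears in the single slope when the within-patient slope is zero: psi·B / (W + psi·B)
- the same share for GEE with independence: B / (W + B)

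The between-patient slope here is the slope on the patient's observed mean. With both ICCs between 0.3 and 0.7, the extremes are:

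| Visits | Mixed model, lowest (ICCx 0.3, ICCy 0.7) | Mixed model, highest (ICCx 0.7, ICCy 0.3) | Independence GEE, ICCx 0.3 | Independence GEE, ICCx 0.7 |
|---|---|---|---|---|
| 3 | 0.200/(1.40+0.200) = 13% | 1.050/(0.60+1.050) = 64% | 1.6/3 = 53% | 2.4/3 = 80% |
| 4 | 0.184/(2.10+0.184) = 8% | 1.142/(0.90+1.142) = 56% | 1.9/4 = 48% | 3.1/4 = 78% |
| 6 | 0.167/(3.50+0.167) = 5% | 1.260/(1.50+1.260) = 46% | 2.5/6 = 42% | 4.5/6 = 75% |

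The blend shrinks as visits increase, but it does not vanish at the full six.

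**Simulation.** Inputs: 480 patients (600 × 0.8, from the 20% loss in Power consideration) and six visits. Assumed: attendance falling at random through 100, 80, 65, 50, 40 and 25%; outcome ICC 0.5; marker ICC 0.3, 0.5 or 0.7; between-patient correlation 0.2, 0.3 or 0.5; true within-patient slope zero. There were 200 runs per setting. Eight of the nine settings finished; marker ICC 0.7 with correlation 0.5 did not. All models adjusted for visit.

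| Model | Mean slope, range over settings | Significant at 5% |
|---|---|---|
| Mixed model, one slope | 0.03 to 0.11 | 27-98% |
| Exchangeable GEE, one slope | 0.03 to 0.11 | 27-99% |
| Independence GEE, one slope | 0.08 to 0.25 | 74-100% |
| Mixed model, deviation term after the split | -0.002 to 0.004 | 1.5-7% |

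The closed form and the simulation agree. At marker ICC 0.5 and correlation 0.3, the one-slope mixed model gave 0.064 and the patient-mean term 0.222, a ratio of 29%. Attendance averages 1 + 0.80 + 0.65 + 0.50 + 0.40 + 0.25 = 3.6 visits. With both ICCs at 0.5 the closed form gives 0.5/(1.0+0.5) = 33% at 3 visits and 0.5/(1.5+0.5) = 25% at 4.

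**The case against.** The strongest reply is that the article never says a single slope is used. It names model classes and leaves covariates, centring and working correlation unstated. It condenses a fuller protocol, and such detail may be there or in an analysis plan. This stands, and it makes the point conditional on how the exposure is entered. It does not remove the point: the article itself gives Research question 2 three targets (change, correlation, level) and an either/or method.

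A reader might infer more than the text supports in three places.

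- *That Research question 3 has the same fault.* It does not show it. After a separate baseline cross-sectional model, the plan says "we will investigate the association between changes in inflammatory markers over time and cachexia severity using mixed linear modelling", so change in the marker is already the named exposure.
- *That Research question 4 has the same fault.* Its method is "We will use repeated measurements and a linear mixed effect model to perform the analyses", and its own objective asks only for association. A blended slope is hard to interpret but contradicts nothing there. The point reaches it only if its result is presented as meeting the Abstract's aim about changes in depression.
- *That GEE is ruled out by the plan's own account of drop-out.* Expected limitations says "These patients cannot be included in the predictive analyses as they are not missing at random and may bias the results", but this concerns patients lost before response is evaluated, not the one-year models. Drop-out truly not at random would also bias an ordinary mixed model. In 30 simulated data sets with drop-out driven by the last pain score and a true week-52 change of -1.50, exchangeable GEE gave -1.52 and the mixed model -1.50. Only independence GEE was clearly off, at -1.86, and the plan does not name that structure. GEE is also open for Research question 2 alone, and choosing a mixed model does not cure the blending.

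Two further limits stand. Research question 2 could also mean that the level of a marker relates to the later course of pain, which is a level-by-time question. And the split removes only confounding that is constant within a patient. Disease severity that changes over time can still move marker and symptom together, and direction of causality stays open.

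**Conclusion.** The point holds for Research questions 2 and 6: their targets are within-patient, and the stated methods do not isolate that association. The stated size of the problem depends on the exposure being entered as one raw covariate and on ICCs that are assumed. The proportion of falsely significant slopes also depends on the assumed between-patient correlation. Contamination was present at every setting examined, and was larger with independence GEE than with a random-intercept model. The consequence is a possible misreading of secondary, exploratory results, which the authors themselves describe as exploratory in character. It should be corrected before those analyses are run.

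**What to change.** For Research questions 2 and 6, first state whether the target is the within-patient association, the between-patient association or both. If a level-by-time question is meant for Research question 2, say so as a separate target. Then:

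1. Include visit as a factor.
2. Enter each time-varying exposure as two terms: the patient's own mean, and the deviation from it at each visit.
3. Report the deviation term as the answer on change and the mean term as the cross-sectional association.
4. Name one model for Research question 2: a mixed model, or GEE with a stated working correlation other than independence.
5. Do the same in Research question 4 if its result is to be read as the Abstract's aim on change in depression.

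The cost is one extra coefficient per model and a sentence or two of text. The interval for the within-patient effect will be wider than for a blended slope. The report should add that the split does not deal with time-varying severity or direction of causality.
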